## Abstract

**Background:**

Etoposide plus cisplatin (EP) combined with concurrent accelerated hyperfractionated thoracic radiotherapy (AHTRT) is the standard treatment strategy for unresectable limited‐disease (LD) small cell lung cancer (SCLC), which has remained unchanged for over two decades. Based on a previous study that confirmed the non‐inferiority of amrubicin (AMR) plus cisplatin (AP) when compared with EP for extensive‐disease (ED) SCLC, we have previously conducted a phase I study assessing AP with concurrent TRT (2 Gy/time, once daily, 50 Gy in total) for LD‐SCLC therapy. Our findings revealed that AP with concurrent TRT could prolong overall survival to 39.5 months with manageable toxicities. Therefore, we plan to conduct a phase I study to investigate and determine the effect of AP combined with AHTRT, recommended dose (RD), maximum tolerated dose (MTD), and dose‐limiting toxicity (DLT) of AP in patients with LD‐SCLC.

**Methods:**

Treatment‐naive patients with LD‐SCLC, age between 20 and 75 years, who had a performance status of 0 or 1 and adequate organ functions will be enrolled. For chemotherapy, cisplatin 60 mg/m^2^/day (day 1) and AMR (day 1 to 3) will be administered with AHTRT (1.5 Gy/time, twice daily, 45 Gy in total). The initial AMR dose is set to 25 mg/m^2^/day. RD and MTD will be determined by evaluating toxicities.

**Discussion:**

Based on our previous study, the initial dose of AMR 25 mg/m^2^ is expected to be tolerated and acceptable. Here, we aim to determine whether treatment with AP and concurrent AHTRT would be an optimal choice with manageable toxicities for LD‐SCLC.

## INTRODUCTION

Small cell lung cancer (SCLC) accounts for ~13% of all lung cancers and is characterized by rapid growth, early metastasis, and high rates of relapse.^1^ Approximately one‐third of patients with SCLC are diagnosed with limited‐disease (LD)‐SCLC, and the treatment for patients with LD‐SCLC involves concurrent chemotherapy and radiotherapy, as <5% of these patients are suitable to undergo radical surgery.^2^, ^3^ Etoposide plus cisplatin (EP) combined with concurrent accelerated hyperfractionated thoracic radiotherapy (AHTRT) is considered the standard treatment for unresectable LD‐SCLC^4^, ^5^, ^6^; however, a high proportion of patients with LD‐SCLC experience disease relapse, accompanied by an insufficient long‐term survival rate. Accordingly, novel strategies are needed to achieve long‐term response and cure in patients with LD‐SCLC.

Amrubicin (AMR), or its active metabolite amurubicinol, exerts an antitumor effect by stabilizing the cleavable complex via topoisomerase II, which results in DNA cleavage and suppresses tumor growth.^7^ In treatment‐naive patients with extensive‐disease (ED)‐SCLC, AMR monotherapy has shown a remarkable improvement in overall response rate (ORR) (75.8%) and median overall survival (OS) (11.7 months).^8^ In addition, a clinical study has revealed the non‐inferiority of AMR plus cisplatin (AP) when compared with EP for treatment‐naive patients with ED‐SCLC in a Chinese population.^9^ These findings suggest the promising antitumor effect of AMR in treatment‐naive ED‐SCLC, which could also be used in LD‐SCLC. We previously conducted a phase I study to assess AP with concurrent TRT (2 Gy/time, once daily, 50 Gy in total) in patients with LD‐SCLC.^10^ Although the obtained results were from a limited patient cohort in a phase I study, AP with concurrent TRT markedly improved OS to 39.5 months. Dose‐limiting toxicities (DLTs) included neutropenia and leukopenia; however, all toxicities were manageable. Although this study indicated the promising results of AP with once‐daily concurrent TRT, no patient could achieve complete response, suggesting that further study will be required to “cure” the patients with LD‐SCLC.

Twice‐daily accelerated hyperfractionated irradiation (ie, 1.5 Gy/time, 5 days a week, 45 Gy in total) could significantly improve OS when compared with once‐daily irradiation (ie, 1.8 Gy/time, once daily, 5 days a week, 45 Gy in total)^4^; hence, the twice‐daily irradiation schedule could be tolerated and potentially prolong survival when combined with AP. Based on the previous studies, we plan to conduct a phase I study of AP combined with AHTRT (1.5 Gy/time, twice daily, 45 Gy in total) and aim to investigate and determine the effect, recommended dose (RD), maximum tolerated dose (MTD), and DLT of AP in patients with LD‐SCLC.

## METHODS

### Study design

This is a phase I, multi‐institutional, single‐arm, interventional study. The study design is shown in Figure 1. We initially plan to enroll three patients and evaluate the emergence of AMR‐related DLTs during the first cycle; the AMR dose is set at 25 mg/m^2^ for the first cycle of chemotherapy. DLTs will be confirmed if any of the following events occur: (i) grade 4 neutropenia or leukopenia for more than 4 days; (ii) grade 4 neutropenia or leukopenia with a fever of >38°C, suggesting an infection; (iii) grade 4 thrombocytopenia; and (iv) grade 3 or higher non‐hematologic toxicities. Adverse events will be assessed according to the National Cancer Institute Common Terminology Criteria for Adverse Events version 5.0.

**FIGURE 1 tca14555-fig-0001:**
[figure not shown]
In the first cycle, AMR 25 (or 20, if reduced) mg/m^2^/day (from day 1 to day 3) and cisplatin 60 mg/m^2^/day (day 1) will be administered. In the following three cycles, AMR 35 mg/m^2^/day (from day 1 to day 3) and cisplatin 60 mg/m^2^/day (day 1) will be administered. The accelerated hyperfractionated thoracic radiotherapy, as 1.5 Gy/time, twice daily, 5 days a week, 45 Gy in total, will be administered concurrently from day 2 of the first chemotherapy cycle

MTD and RD will be determined as shown in Figure 2. (1) If DLTs are not observed in the initial three patients, we plan to add six patients as the extension study. The 25 mg/m^2^ of AMR will be determined as MTD and RD. (2) If DLTs are confirmed in one of the first three patients enrolled, we will add three additional patients at 25 mg/m^2^ of AMR to evaluate DLTs further. (2)‐1: If DLTs are confirmed in none of the additional three patients, we will add six additional patients as the extension study. The 25 mg/m^2^ of AMR will be determined as MTD and RD. (2)‐2: If DLTs are confirmed in more than one of the additional three patients, the study will be finished. The 25 mg/m^2^ of AMR will be determined as MTD and the 20 mg/m^2^ of AMR will be determined as RD. (3) If DLTs are confirmed in more than two of the first three patients, we plan to add three patients to receive a reduced dose of 20 mg/m^2^. (3)‐1: If DLTs are confirmed in none of the additional three patients, the 20 mg/m^2^ of AMR will be determined as MTD and RD. (3)‐2: If DLTs are confirmed in more than one of the additional three patients, the study will be considered to terminate.

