**FIGURE 2 tca14555-fig-0002:**
[figure not shown]
The schema of the method to determine RD and MTD in ACIST study. If DLTs are not observed in the initial three patients, we plan to add six patients. The 25 mg/m^2^ of AMR will be determined as MTD and RD. If DLTs are confirmed in one of the first three patients enrolled, we will add three additional patients at 25 mg/m^2^. If DLTs are confirmed in none of the additional three patients, we will add six additional patients. The 25 mg/m^2^ of AMR will be determined as MTD and RD. If DLTs are confirmed in more than one of the additional three patients, the 25 mg/m^2^ of AMR will be determined as MTD and the 20 mg/ml of AMR will be determined as RD. If DLTs are confirmed in more than two of the first three patients, we plan to add three patients to receive a reduced dose of 20 mg/m^2^. If DLTs are confirmed in none of the additional three patients, the 20 mg/m^2^ of AMR will be determined as MTD and RD. If DLTs are confirmed in more than one of the additional three patients, the study will be considered to terminate

All patients enrolled in the study will provide written informed consent, and the study will be conducted in accordance with the Declaration of Helsinki and Good Clinical Practice Guidelines. The study protocol was reviewed and approved by the clinical review board of Nagasaki University (CRB7180001). This study was registered in the Japan Registry of Clinical Trials (no. jRCT1071200033) on September 30, 2020.

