### Endpoints

The primary endpoint of the present study is to determine RD, and secondary endpoints are evaluating the response rate (RR), OS, progression‐free survival (PFS), MTD, DLTs and adverse effects. Efficacy will be assessed according to the Response Evaluation Criteria in Solid Tumors ver.1.1. PFS is defined as the time from the start date of chemotherapy to disease progression or death from any cause, whereas OS is defined as the time from the start date of chemotherapy to the last day confirmed to be alive or dead from any cause.

The Kaplan–Meier method will be used to estimate PFS and OS. Survival analysis will be conducted at the end of the follow‐up period. STATA SE version 16.1 (Stata Corp) will be used to perform analyses.

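### The published dose rules fix 25 mg/m² as the recommended dose whatever DLTs occur in the six extension patients, who are 6 of 9 or 6 of 12 at that dose

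*Protocol article*

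**What the plan says.** The Endpoints section states: "The primary endpoint of the present study is to determine RD". MTD, DLTs and adverse effects are secondary endpoints. The Abstract adds: "RD and MTD will be determined by evaluating toxicities".

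The decision tree is in Methods, Study design, and is repeated in the Figure 2 caption. The first cohort has three patients at amrubicin 25 mg/m², with DLTs assessed in cycle 1. The relevant branches are:

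- **Rule (1), 0/3 DLTs:** "If DLTs are not observed in the initial three patients, we plan to add six patients as the extension study". The next sentence names 25 mg/m² as MTD and RD.
- **Rule (2)-1, 1/3 and then 0/3 DLTs:** "If DLTs are confirmed in none of the additional three patients, we will add six additional patients as the extension study". The same sentence on MTD and RD follows. The Figure 2 caption agrees: "If DLTs are confirmed in none of the additional three patients, we will add six additional patients".
- **Rule (2)-2, 1/3 and then more DLTs:** "If DLTs are confirmed in more than one of the additional three patients, the study will be finished". The MTD is then 25 mg/m² and the RD 20 mg/m².

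The DLT definition opens with "DLTs will be confirmed if any of the following events occur". No sentence gives a threshold, pooled rate, stopping rule or de-escalation rule for the six extension patients.

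**The concern.** The text does not say whether the RD is declared before or after the extension. If before, the extension DLTs come too late to count. If after, no criterion uses them. Either way the RD is 25 mg/m².

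This sits badly with the rest of the plan. The extension supplies two thirds of the patients at 25 mg/m² under rule (1) and half under rule (2)-1. The decision itself can rest on 0/3 or 1/6 DLTs, whose exact 95% upper limits are 71% and 64%. Rule (2)-2 shows that the plan leaves 25 mg/m² at some observed DLT rate in six patients, yet the same or a higher rate pooled over nine or twelve changes nothing. The Discussion says that the 25 mg/m² dose came from a study with once-daily radiotherapy, so its tolerability with the twice-daily schedule is the open question.

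The trial could therefore report 25 mg/m² as RD against its own pooled toxicity data, with no written rule to settle the conflict.

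**Working it through.** The article gives no target DLT rate, power or sample-size calculation, so there is no figure to reproduce. The true DLT rate p at 25 mg/m² is an assumption, taken from 0.20 to 0.50.

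**Inputs from Study design.** Cohorts of 3; extension of 6; 25 mg/m² selected after 0/3, or after 1/3 and then 0/3.

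**Patients at the dose.** Rule (1): 3 + 6 = 9, of whom 6 (67%) are extension patients. Rule (2)-1: 3 + 3 + 6 = 12, of whom 6 (50%) are.

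**Worst counts that still give RD = 25.** 0/3 + 6/6 = 6/9 (67%), and 1/6 + 6/6 = 7/12 (58%).

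**When rule (2)-2 leaves the dose.** The first cohort has 1 DLT. Read literally, two or three of the next three must have a DLT, so the total is at least 3/6. If at least one was meant, the total is at least 2/6.

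**Chance that the published rules select 25 mg/m².** P(RD = 25) = (1−p)³ + 3p(1−p)² × (1−p)³. It is the same under both readings of rule (2)-2, because rule (2)-1 needs zero DLTs in the second cohort. At p = 0.30: 0.343 + 0.441 × 0.343 = 0.343 + 0.151 = 0.494.

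**Extension DLTs.** Let X be Binomial(6, p). The pooled result is X/9 under rule (1) and (1+X)/12 under rule (2)-1. On both paths:

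- pooled rate at least 1/2 means X ≥ 5 (5/9 or 6/12);
- pooled rate above 1/3 means X ≥ 4 (4/9 or 5/12);
- pooled rate at least 1/3 means X ≥ 3 (3/9 or 4/12).

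Each joint probability is P(RD = 25) × P(X ≥ k). At p = 0.30 and k = 4: 0.494 × 0.0705 = 0.035.

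| Assumed p | 0.20 | 0.30 | 0.40 | 0.50 |
|---|---|---|---|---|
| P(RD = 25) as published | 70.9% | 49.4% | 30.9% | 17.2% |
| RD = 25 and pooled ≥ 1/2 | 0.1% | 0.5% | 1.3% | 1.9% |
| RD = 25 and pooled > 1/3 | 1.2% | 3.5% | 5.5% | 5.9% |
| RD = 25 and pooled ≥ 1/3 | 7.0% | 12.6% | 14.1% | 11.3% |
| P(RD = 25) if confirmed only at ≤ 3/9 or ≤ 4/12 | 69.7% | 45.9% | 25.4% | 11.3% |
| P(RD = 25) if confirmed only at ≤ 2/9 or ≤ 3/12 | 63.9% | 36.8% | 16.8% | 5.9% |

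The third row is what a limit of at most 1/3 changes; the fifth is the first minus the third. The fourth row is what a limit strictly below 1/3 changes; the sixth is the first minus the fourth.

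**The case against.** The strongest reply is that the plan separates two purposes: dose finding in three or six patients, then an extension that informs response, survival and adverse effects. Extension toxicity is followed up, and not reopening the dose is a design choice that many phase I trials make. This does not rescue the rule. The Abstract ties the RD to evaluation of toxicities, and rule (2)-2 already leaves 25 mg/m² at pooled rates below 6/9 or 7/12. The reply does rule out one inference: the text does not show that extension toxicity goes uncollected. It shows only that it has no stated bearing on the RD.

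Three further points stand.

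- **Size.** A reader might take the 7% to 14% row as the harm that the proposed limit removes. It is not. That row includes exactly 3/9 and 4/12, which the limit still accepts. On the literal reading of rule (2)-2, the chance of reaching that rule's own level (at least 1/2) is under 2%.
- **Cut-off.** The article gives no target DLT rate, so nothing in it selects 1/3 over a neighbouring limit.
- **Condensed source.** A reader might infer that the trial has no extension rule at all. The full protocol and the Figure 2 graphic are not shown, so that cannot be said. The silence still matters, because the article sets out these branches and their outcomes twice instead of deferring them.

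**Conclusion.** The point holds for the published text. Rules (1) and (2)-1 and the Figure 2 caption make the primary endpoint insensitive to DLTs in half to two thirds of the patients at the selected dose. That follows from the wording and needs no assumed rate.

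The practical size is modest. With a confirmation limit of at most 1/3, the RD would change in 1.2%, 3.5%, 5.5% and 5.9% of trials at true DLT rates of 0.20, 0.30, 0.40 and 0.50. These rates are assumptions, and the figures treat patients as independent with a common DLT rate. Nothing here shows that 25 mg/m² is too toxic or that the trial is likely to pick the wrong dose.

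This should be fixed, because it concerns the primary-endpoint rule and is cheap to close. Confidence is medium, because the full protocol may contain a rule.

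**What to change.** In rules (1) and (2)-1 and in Figure 2:

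1. Call 25 mg/m² a provisional RD at the point where the extension opens.
2. State that the first-cycle DLT criteria in Study design apply to the six extension patients.
3. Confirm 25 mg/m² only if pooled DLTs are at most 3/9 under rule (1) or 4/12 under rule (2)-1.
4. Otherwise follow rule (2)-2: MTD 25 mg/m², RD 20 mg/m².
5. Report the pooled DLT rate at 25 mg/m² with an exact confidence interval.

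The sponsor should settle the wording of rule (2)-2 first. If at least one DLT was meant there, that rule leaves the dose at 2/6, and the consistent limit is below 1/3: at most 2/9 or 3/12.

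**Cost.** This is amendment wording and needs no extra patients, since the six are already planned. The RD is declared later. At a true rate of 0.20, P(RD = 25) falls from 70.9% to 69.7%, and at 0.30 from 49.4% to 45.9%. The stricter limit costs more when the dose is tolerable: 63.9% at 0.20 and 36.8% at 0.30. After a failed check, 20 mg/m² would be untested in this trial, as rule (2)-2 already accepts. If the sponsor prefers to test it first, as rule (3) does, that takes three more patients.

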### Interventions

#### Chemotherapy

In the first cycle, AMR 25 (or 20, if reduced) mg/m^2^/day (from day 1 to day 3) and cisplatin 60 mg/m^2^/day (day 1) will be administered. In the following three cycles, AMR 35 mg/m^2^/day (from day 1 to day 3) and cisplatin 60 mg/m^2^/day (day 1) will be administered (Figure 1).

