In another study examining the consolidation of three cycles of AP after one cycle of EP with AHTRT, the authors documented an impressive 5‐year OS rate of 57.8%, suggesting the therapeutic potential of AP combined with AHTRT. The incidence of grade 3/4 neutropenia was 100%, whereas that of febrile neutropenia was 43%; however, all observed adverse effects were manageable with granulocyte‐colony stimulating factor support.^13^ It should be noted that the dose of AMR was set at 40 mg/m^2^ according to the RD from the phase I‐II study of AP for treatment‐naive ED‐SCLC,^14^ however, dose reduction was required in 33% of patients, implying that dose of 40 mg/m^2^ AMR might be too toxic for the patients with LD‐SCLC who will receive AP combined with AHTRT. Considering the toxicities associated with AMR, the RD of AMR with once‐daily TRT was evaluated from 20 mg/m^2^ in a dose‐escalation manner, and the RD of AMR was determined as 25 mg/m^2^ in our previous study.^7^ Following the introduction of twice‐daily irradiation, we plan to undertake a dose de‐escalation approach from 25 mg/m^2^ to determine the RD of AMR with twice‐daily AHTRT, based on our previous phase I study, which showed that doses of 25 mg/m^2^ AMR and 60 mg/m^2^ cisplatin are recommended for AP combined with TRT (2 Gy/day, once‐daily).^10^ We also set to raise the dose of AMR to 35 mg/m^2^ from second to fourth cycles of AP because AHTRT will finish during the first cycle of AP in this protocol. In a phase III study, which compared the efficacy of AP and that of IP in treatment naive Japanese patients with ED‐SCLC, the dose of AMR was reduced from 40 mg/m^2^ to 35 mg/m^2^ because of the high incidence of severe hematological toxicities.^15^ Furthermore, our retrospective study revealed that the real‐world incidence rate of febrile neutropenia among patients with thoracic malignancies that were treated with single‐agent AMR chemotherapy was 30%.^16^ Based on these findings for Japanese patients, the dose of 35 mg/m^2^ AMR from second cycle to fourth is predicted as the suitable dose in this protocol.

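### The MTD label changes meaning between decision branches, and a tolerated 25 mg/m² is called the MTD although no higher first-cycle dose is tested

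*Protocol article*

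**What the plan says.** The rules are in the protocol article, Methods, Study design (the text after the Figure 1 legend), and the Figure 2 legend repeats them.

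- **Scope of the assessment.** The plan evaluates "related DLTs during the first cycle; the AMR dose is set at 25 mg/m^2^ for the first cycle of chemotherapy". The Chemotherapy section allows two levels there: "In the first cycle, AMR 25 (or 20, if reduced) mg/m^2^/day". The Discussion describes the approach as de-escalation from 25 mg/m².
- **Branch (1).** "If DLTs are not observed in the initial three patients, we plan to add six patients as the extension study". The label for 25 mg/m² follows, and then the next branch begins: "of AMR will be determined as MTD and RD. (2) If DLTs are confirmed in one of the first three patients enrolled".
- **Branch (2)-1.** One DLT in the first three patients and none in the next three: 25 mg/m² is again both MTD and RD.
- **Branch (2)-2.** One DLT in the first three and further DLTs in the next three. The study ends, and the 25 mg/m² level "of AMR will be determined as MTD and the 20 mg/m^2^ of AMR will be determined as RD".
- **Branch (3)-1.** 25 mg/m² fails in the first three patients and three more at 20 mg/m² have no DLT: "the 20 mg/m^2^ of AMR will be determined as MTD and RD".

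The Endpoints section makes the RD primary and lists the MTD among the secondary endpoints. The Introduction also names the MTD as an aim.

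**The concern.** An MTD label should mean the same thing whichever way the data fall. Here a failure of 25 mg/m² leads to an MTD of 25 in one branch and of 20 in another.

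In the two favourable branches the label has a different weakness. A starting dose that passes, with nothing higher examined, gives a lower bound for the MTD and does not locate it.

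At stake is the conclusion on a named secondary endpoint, which a later study of this combination might cite. The recommended dose is not at stake.

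**Working it through.** **Inputs.** The dose levels, DLT window and branch rules come from Study design, Chemotherapy and the Figure 2 legend. The article gives no target or expected DLT rate, so there is no planned figure to reproduce. The Abstract says only that 25 mg/m² is expected to be tolerated. The true DLT probability *p* at 25 mg/m² is therefore an assumption, shown from 0.05 to 0.30.

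**Step 1: the branches side by side.** The thresholds 'more than one' and 'more than two' are read here as 'one or more' and 'two or more', the reading under which the branches cover every outcome.

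| Branch | DLTs at 25 mg/m² | 25 mg/m² | MTD | RD |
|---|---|---|---|---|
| (1) | 0/3 | passes | 25 | 25 |
| (2)-1 | 1/3, then 0/3 | passes | 25 | 25 |
| (2)-2 | 1/3, then 1 or more of 3 | fails | 25 | 20 |
| (3)-1 | 2 or more of 3 (then 0/3 at 20) | fails | 20 | 20 |

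**Step 2: try each usual meaning of MTD.**
- *Highest tested dose that passed:* fits (1), (2)-1 and (3)-1, but not (2)-2.
- *Dose that proved too toxic:* fits (2)-2, but not (1), (2)-1 or (3)-1.

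Neither fits all four. A cut-off on the observed DLT proportion does not help on this reading: 1 + 3 = 4 of 6 in (2)-2 and 2 of 3 in (3) are both 67%, yet the MTDs differ.

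**Step 3: how often each label arises.** With independent patients and DLT probability *p*:
- P(1) = (1−p)³
- P(2-1) = 3p(1−p)² × (1−p)³ = 3p(1−p)⁵
- P(2-2) = 3p(1−p)² × [1 − (1−p)³]
- P(2-2), thresholds taken literally = 3p(1−p)² × [3p²(1−p) + p³]

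Worked at p = 0.30:
- (1) + (2)-1: 0.343 + 0.151 = 0.494
- (2)-2: 0.441 × 0.657 = 0.290
- (2)-2, literal: 0.441 × 0.216 = 0.095

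| p | P(1) | P(2-1) | (1) or (2)-1 | (2)-2 | (2)-2, literal |
|---|---|---|---|---|---|
| 0.05 | 0.857 | 0.116 | 0.973 | 0.019 | 0.001 |
| 0.10 | 0.729 | 0.177 | 0.906 | 0.066 | 0.007 |
| 0.20 | 0.512 | 0.197 | 0.709 | 0.187 | 0.040 |
| 0.30 | 0.343 | 0.151 | 0.494 | 0.290 | 0.095 |

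The column for (1) or (2)-1 does not depend on how the thresholds are read. It falls below one half at p of about 0.297.

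These are not the total probabilities of an MTD of 25. Adding (2)-2 gives P(at most 1 DLT in 3) = 0.993, 0.972, 0.896 and 0.784 at the four rates.

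**The case against.** Much of the case on the other side stands.

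- **The pair of results is informative.** Every branch that sets an MTD also sets an RD. MTD 25 with RD 25 means tolerated, and MTD 25 with RD 20 means not tolerated. DLTs are themselves a secondary endpoint. A reader might infer that the two meanings of an MTD of 25 could not be told apart, but anyone who sees the RD can separate them.
- **The later cycles are explained.** A reader might see a further contradiction in the dose for cycles 2 to 4 ("In the following three cycles, AMR 35" mg/m²), which exceeds an MTD of 25. The documents do not support this. The Introduction ties the MTD to treatment combined with accelerated hyperfractionated thoracic radiotherapy (AHTRT), Study design limits DLT assessment to cycle 1, and the Discussion explains that the later dose differs because the radiotherapy ends during cycle 1.
- **The starting dose is justified.** The authors' earlier study escalated from 20 mg/m² and arrived at 25 as the RD, and stepping down from there is a stated choice. That study used once-daily radiotherapy, however, and the article reports no MTD from it, so it gives no upper bound for the twice-daily schedule.
- **A definition may exist in the full protocol.** Its absence from an article is no fault. The point rests on the labels that the article does state, and neither usual definition would reconcile (2)-2 with (3)-1.

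**Conclusion.** The point holds as an inconsistency in stated rules plus an unsupported label. The conflict between (2)-2 and (3)-1 needs no assumption about DLT rates. In (1) and (2)-1 the data support only the statement that the highest dose tested was tolerated.

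It is tempting to call the MTD in those two branches wrong. That goes too far: 25 mg/m² might still be the true MTD, and the design simply cannot show it.

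The unsupported label arises with probability 0.97, 0.91, 0.71 or 0.49 at assumed DLT rates of 0.05, 0.10, 0.20 or 0.30. Branch (2)-2 arises with probability 0.07, 0.19 or 0.29 at rates of 0.10, 0.20 or 0.30 on the 'one or more' reading, and 0.095 at 0.30 on the literal text. All these figures rest on assumed rates, and the article states no toxicity limit to set them against.

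The importance is moderate. The label and conclusion of a secondary endpoint are affected. The primary endpoint (RD), the doses, enrolment and stopping do not depend on the label.

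**What to change.** 1. State one definition of MTD and apply it in every branch, so that (2)-2 and (3)-1 agree in both Study design and the Figure 2 legend. Which definition to use is for the investigators. If it is the highest tested dose that passed, note that (2)-2 ends without any patient treated at 20 mg/m², so the MTD there cannot simply be relabelled as 20.
2. Where the highest tested dose passes, as in (1) and (2)-1, report that the MTD was not reached and that no higher dose was tested with AHTRT. The RD statement stays as it is.

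The cost is a change of wording in the decision rules and the legend, and a more modest MTD conclusion. It needs no extra patients and changes no dose, enrolment step or stopping rule.

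### Rule (2)-2 declares 20 mg/m² the recommended dose without any patient having received 20 mg/m² with twice-daily radiotherapy

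*Protocol article*

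**What the plan says.** The Endpoints section names the objective: "The primary endpoint of the present study is to determine RD". The Discussion narrows it to the radiotherapy schedule under study: the trial de-escalates from 25 mg/m² "to determine the RD of AMR with twice‐daily AHTRT".

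The rules are in Methods, Study design, and again in the Figure 2 legend. Three patients start at 25 mg/m². If one has a DLT, three more are treated at 25 mg/m². Rule (2)-2 then reads: "If DLTs are confirmed in more than one of the additional three patients, the study will be finished". It goes on to make 25 mg/m² the MTD and states that "the 20 mg/m^2^ of AMR will be determined as RD". The legend repeats this with a misprinted unit ("the 20 mg/ml of AMR will be determined as RD") and shows no cohort at the lower dose.

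Rule (3), for heavier toxicity in the first three patients, is the only place where anyone receives 20 mg/m²: "we plan to add three patients to receive a reduced dose of 20 mg/m^2". The condition for accepting that dose is explicit: "If DLTs are confirmed in none of the additional three patients, the 20 mg/m^2^ of AMR will be determined as MTD and RD".

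**The concern.** In one branch the study stops and reports, as its primary result, a dose that it never gave with AHTRT. In another branch the same dose has to show no DLT in three patients before it may carry the same label. The article does not say why one route needs data at 20 mg/m² and the other needs none.

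What is at stake is the meaning of the conclusion. A later trial of amrubicin plus cisplatin with AHTRT could take 20 mg/m² as a tested RD when it is an extrapolation. The Discussion describes this as the first study to give the combination with AHTRT from cycle 1, so there is no other experience with this regimen to fall back on.

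**Working it through.** **Patients treated at the declared RD before any extension cohort**, counted from the rules:

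| Route | Declared RD | Patients at that dose |
|---|---|---|
| (1) | 25 mg/m² | 3 |
| (2)-1 | 25 mg/m² | 3 + 3 = 6 |
| (2)-2 | 20 mg/m² | 0 |
| (3)-1 | 20 mg/m² | 3 |

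This count is the finding. It does not depend on how the thresholds are read or on any assumed rate.

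**How often the branch would arise.** The article states no DLT rate, so there is no figure of its own to reproduce. Let *p* be the true DLT rate at 25 mg/m², assumed to be 0.2, 0.3 or 0.4. The threshold in (2)-2 is more than one of three. Literally that is two or more, but it may be meant as one or more, so both are shown.

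- Entry to rule (2), one DLT in three: 3p(1−p)² = 0.384, 0.441, 0.432.
- Two or more DLTs in the next three: 3p²(1−p) + p³ = 0.104, 0.216, 0.352.
- One or more DLTs in the next three: 1 − (1−p)³ = 0.488, 0.657, 0.784.

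Multiplying the first line by the second or the third:

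| *p* | (2)-2 as worded | (2)-2 if one or more |
|---|---|---|
| 0.2 | 0.384 × 0.104 = 0.040 | 0.384 × 0.488 = 0.187 |
| 0.3 | 0.441 × 0.216 = 0.095 | 0.441 × 0.657 = 0.290 |
| 0.4 | 0.432 × 0.352 = 0.152 | 0.432 × 0.784 = 0.339 |

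**Share of moves from 25 to 20 mg/m² that take the untested route**, P(2-2) / [P(2-2) + P(3)]. Rule (3) is triggered by more than two of the first three, which literally means three of three, with probability p³ = 0.008, 0.027, 0.064. If it means two or more, the probability is 0.104, 0.216, 0.352.

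- Thresholds read as one or more and two or more: 0.187/(0.187 + 0.104) = 64%; 0.290/(0.290 + 0.216) = 57%; 0.339/(0.339 + 0.352) = 49%.
- Thresholds as worded: 0.040/(0.040 + 0.008) = 83%; 0.095/(0.095 + 0.027) = 78%; 0.152/(0.152 + 0.064) = 70%.

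The as-worded shares leave out trials with exactly two DLTs in the first three, which no rule then covers: 3p²(1−p) = 0.096, 0.189, 0.288. The first set of shares has no such gap and is the fairer guide.

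**What the check in rule (3) would do here.** Let *q* be the true DLT rate at 20 mg/m², assumed to be 0.1, 0.2 or 0.3. The chance of no DLT in three is (1−q)³ = 0.729, 0.512, 0.343. The dose would therefore fail to show a clean cohort in 27%, 49% or 66% of trials. Rule (2)-2 accepts it every time.

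**The case against.** The strongest defence is that (2)-2 is a deliberate and familiar choice: once a dose is too toxic, the next-lower level is recommended. Here that level is below a dose just given with AHTRT to six patients, and it was the starting level of the sponsor's earlier escalation study, which went on to recommend 25 mg/m². The contrast with rule (3) can also be read as graded caution. As worded, rule (3) follows three DLTs in three patients, whereas (2)-2 follows three or four in six. No patient in this study is endangered, since the rule stops treatment. A condensed article may also leave its reasoning to the full protocol.

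Much of this stands. The extrapolation is reasonable, the two routes need not be identical, and only one branch is affected. It does not justify calling the dose determined. Naming the next-lower level in an escalation study normally presumes that patients have already received that level on the same regimen. This study descends from 25 mg/m², so nobody in it has. The earlier experience at 20 mg/m² was with once-daily radiotherapy, and reaching (2)-2 would itself show that the once-daily recommendation of 25 mg/m² had not carried over to AHTRT. The rule is stated in full in both text and legend, so the problem is its content and not a missing explanation.

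**Conclusion.** The concern holds. Followed as written, rule (2)-2 reports an RD, the primary endpoint, supported by no patient at that dose with AHTRT. Rules (1), (2)-1 and (3) are not affected by this point.

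The frequencies above rest entirely on assumed DLT rates and on how the thresholds are read. Over the assumed range the branch runs from uncommon to about one trial in three, so it cannot be dismissed as remote. It should be fixed: the affected conclusion is confined to one branch and concerns a lower dose, but there it changes what the trial may claim.

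**What to change.** **Wording change (sufficient on its own).** In rule (2)-2 and the Figure 2 legend, state that 25 mg/m² is not recommended, that 20 mg/m² is the next-lower level and has not been tested with AHTRT, and that the RD is not determined in this study. Correct the unit in the legend in the same edit. This costs no patients and no time. The downside is a less favourable conclusion in that branch, with no added data.

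**Cohort option, if the sponsor wants an RD in this branch.** Treat three patients at 20 mg/m², as rule (3) does, before naming that dose. The outcome of exactly one DLT in three must be settled, because rule (3) leaves it open as worded (it is covered only if more than one is meant as one or more). At an assumed rate of 0.2, that outcome occurs in 3 × 0.2 × 0.8² = 38% of trials. Either no RD is declared, or three more patients are treated at 20 mg/m². The branch total becomes 6 + 3 = 9 patients, or 6 + 3 + 3 = 12 with expansion, against 3 + 3 + 6 = 12 already possible under (2)-1. The added cohort is only a weak check: no DLT in three has a one-sided 95% upper bound of 1 − 0.05^(1/3) = 63%.

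The choice between the two is the sponsor's.
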